### Economic evaluation

This study serves as a preliminary investigation for economic evaluation in tandem with a clinical trial, in which an additional analysis of costs is conducted based on the outcomes of the clinical trial. Depending on the results of the clinical trial, a cost-minimization analysis or cost-utility analysis is planned. The analysis period is identical to that of the clinical trial based on the results of the fourth and eighth weeks. The perspective of the analysis is based on the healthcare system.

The costs are calculated by combining the frequency of treatments and unit costs; the primary cost components comprise direct medical costs, direct non-medical costs (transportation costs and nursing costs), and indirect costs (costs of productivity loss and time costs). Cost data are obtained using clinical trial institution data and a self-developed medical use survey form (loaded in the electronic CRF), and costs that cannot be obtained from research subjects or clinical trial institution data are estimated based on other statistical indicators.

EuroQol 5-dimension (EQ-5D) was used for the economic evaluation analysis. The EQ-5D is an indicator that indirectly measures quality weights reflecting individual preferences and evaluates general health status (quality of life) through five items (mobility, self-care, usual activities, pain/discomfort, and anxiety/depression). The EQ-5D-5L, an enhancement of the EQ-5D-3L that was developed by the EuroQol Group in 1990, was developed in 2009 [20]. In this study, the Korean version of the EQ-5D-5L with proven validity is utilized. A validity study was conducted according to the standard protocol set by the EuroQol Group, and quality-adjusted life years were calculated based on the value assessment results of Kim et al. (2016), which had representative samples [21].

All trial participants participating in the clinical trial are required to self-complete the EQ-5D at baseline, week 4, and week 8. If adverse effects are observed, additional follow-up surveys should be conducted. In addition, the measurement results collected as clinical effectiveness evaluation variables in this clinical trial (measurements at baseline, week 4, and week 8) can also be included in the analysis if necessary.

If there is no difference between the groups in the clinical research results including side effects, a cost-minimization analysis is performed, and the results of all cost items surveyed (total cost) are analyzed. If there is a difference between groups in the results of the clinical research, a cost-effectiveness analysis is conducted to present the incremental cost-effectiveness ratio (ICER), and at the same time, the total cost and total utility of each group intervention is presented to confirm the overall scale. The ICER is calculated by dividing the increment in cost compared with the control group by the increment-in-effect. As only the cost and effect of the current year are considered, no discount rate is applied. If necessary, univariate sensitivity analysis is performed for uncertain variables related to cost and effect.

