In this study, the primary outcome is the change in FEV_1_, with a significance level (α) set at 0.05 and a test power (1-β) set at 0.8. The number of participants was determined using g-power, considering a two-sided test and an allocation ratio of 1:1 [11]. As a result, the effect size was calculated to be 0.437, and the total number of participants was 168. Taking into account the number of recruitable participants, the minimum scope for validity assessment, and a dropout rate of 15%, the total number of participants was determined to be 198 to secure the minimum necessary sample size.

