### Statistical analysis

#### Effectiveness outcomes

Statistical analyses are conducted independently by a statistical expert using SAS. In the two-tailed tests, the level of significance is set at 0.05. All analyses primarily utilize intention-to-treat analysis, with per-protocol analysis conducted concurrently, and the results are presented together. In the demographic baseline data, continuous variables are presented as mean and standard deviation and are analyzed using an independent t-test or Mann–Whitney U test. Categorical variables are presented as frequency and proportion and analyzed using a chi-square test or Fisher's exact test (when the expected frequency is less than 5 in more than 25% of all values).

The primary efficacy evaluation is based on the mean change in FEV_1_ scores evaluated at week 8 (56 days post-dosing), whereas secondary efficacy evaluations compare the means of PEF, FVC, FEF25–75, FeNO, ACT scores, AQLQ scores, Serum IgE, eosinophil count, CRP, and the frequency of rescue medication use assessed at baseline and weeks 4 and 8. If the assumption of normality is satisfied, an independent t-test is conducted; otherwise, the Mann–Whitney U test is applied. However, if significant differences between the groups are found in baseline values, an analysis of covariance (ANCOVA) is performed. Missing data is replaced using the last observation carried forward method; each missing value is replaced with the participant's last observed value. For the secondary efficacy evaluation, the distribution of participants according to each diagnosis of Korean medicine pattern identification assessed at baseline is presented as frequency and proportion and visualized in tables or graphs through descriptive analysis.

Subgroup analysis will be performed according to the following criteria: First, subgroups will be divided according to the type of asthma medication (ICS or ICS + LABA) taken in addition to the LTRA at enrollment. Second, the effect will be further analyzed by age, separating younger patients (< 35 years) from older patients (> 60 years). Third, subgroups will be defined as male and female. Fourth, subgroups will be created based on severity as measured by ACT, ≤ 15 and > 15. Finally, subgroup analyses will be performed according to Korean medicine pattern identification.

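### The economic evaluation drops to a cost-only comparison when the clinical results show no difference, yet the plan has no criterion for that and no means of showing equal effect

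*Protocol article*

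**What the plan says.** The Economic evaluation section makes the choice of method conditional on the trial's outcome: "Depending on the results of the clinical trial, a cost-minimization analysis or cost-utility analysis is planned". The Abstract repeats the either/or choice. The rule for the first branch is "If there is no difference between the groups in the clinical research results including side effects, a cost-minimization analysis is performed"; this branch analyses total cost. The rule for the second is "If there is a difference between groups in the results of the clinical research, a cost-effectiveness analysis is conducted to present the incremental cost-effectiveness ratio", with each group's total cost and total utility presented alongside. The first passage calls the alternative a cost-utility analysis and the second a cost-effectiveness analysis.

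The section does not say which endpoint, which size of difference or which test decides between the branches. Elsewhere, the article describes only tests of difference: t-test, Mann–Whitney or ANCOVA for efficacy and laboratory values, and chi-square or Fisher for adverse reactions. On the level it says: "In the two-tailed tests, the level of significance is set at 0.05". The sample size is for superiority on FEV1 change, "with a significance level (α) set at 0.05 and a test power (1-β) set at 0.8". The EQ-5D-5L is completed by all participants at baseline, week 4 and week 8, but is not among the outcomes listed for efficacy testing.

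**The concern.** A cost-minimisation analysis compares costs alone, which is sound only when the effects have been shown to be equal. A superiority trial that fails to find a difference has not shown that. Without a margin or another criterion, the natural way to operate the rule is to read a failed difference test as equality.

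Both arms keep the same background asthma therapy and differ only in the added Chungsangboha-tang (CSBHT) or placebo. Entering the cost-only branch after missing a real effect sets any QALY gain to zero and tends to favour the arm without the cost of the added drug. The measure that matters for a QALY analysis, EQ-5D utility, is not tested in the efficacy plan, so its estimate could be left out because of what other endpoints showed. Cost-effectiveness is one of the trial's stated aims, and the Introduction expresses the hope that the work may lead towards insurance coverage.

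**Working it through.** **Inputs.** Sample size section and Table 2: FEV1 before/after of 0.88 ± 0.30 / 1.72 ± 0.75 L (test) and 0.89 ± 0.25 / 1.37 ± 0.80 L (control); pre-post correlation set to zero; two-sided alpha 0.05; power 0.80; 1:1 allocation; 15% dropout.

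**1. Reproducing the plan's figure.**
- SD of change, test: √(0.30² + 0.75²) = 0.808 L. Control: √(0.25² + 0.80²) = 0.838 L. Pooled: √((0.808² + 0.838²)/2) = 0.823 L.
- Mean changes: 1.72 − 0.88 = 0.84 L and 1.37 − 0.89 = 0.48 L, a difference of 0.36 L.
- Effect size: 0.36/0.823 = 0.437. The noncentral-t calculation gives 84 per arm, 168 in total (power 0.804), and 168/0.85 rounds up to 198.

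This agrees with the article: "the effect size was calculated to be 0.437, and the total number of participants was 168". The text prints the control change as 0.39 L, which does not match Table 2, but the stated effect size uses 0.48 L, so the sample size stands.

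**2. What a non-significant FEV1 result leaves open.**
- Standard error at 84 per arm: 0.823 × √(2/84) = 0.127 L.
- 95% CI half-width: 1.974 × 0.127 = 0.251 L, and 0.251/0.36 is about 70% of the planned effect.
- At 99 per arm (198/2, if all randomised participants are analysed) the half-width is 0.231 L.

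**3. How often FEV1 is non-significant when there is a real effect.** Noncentral t, noncentrality = (true difference/0.823) × √(n/2). For 0.18 L at 84 per arm this is 0.219 × √42 = 1.42, against a critical value of 1.974.

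| True difference | Non-significant, 84 per arm | Non-significant, 99 per arm |
|---|---|---|
| 0.36 L (planned) | 20% | 14% |
| 0.25 L | 50% | 43% |
| 0.18 L (half) | 71% | 67% |
| 0.10 L | 88% | 86% |

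**4. Could the trial show equivalence on FEV1?** The documents give no margin, so the margins here are assumptions. For two one-sided 5% tests with true difference 0, n per arm for 80% power is 2 × (0.823 × (1.645 + 1.282)/margin)², and power at 84 per arm is 2Φ(margin/0.127 − 1.645) − 1, or zero where that is negative.

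| Assumed margin | Needed per arm | Power at 84 per arm |
|---|---|---|
| 0.36 L | 90 | 77% |
| 0.20 L | 291 | 0 |
| 0.15 L | 516 | 0 |
| 0.10 L | 1161 | 0 |

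**5. Sensitivity to the SD.** At assumed SDs of 0.5 and 0.3 L, the half-width at 84 per arm falls to 0.152 and 0.091 L. The interval narrows, but without a margin a non-significant result still does not establish equality.

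**The case against.** **The criterion.** The text speaks of no difference, not of a non-significant test. A reader might infer that the protocol states outright that non-significance proves equal effect. It does not. That reading is an inference, though a well-supported one, because tests of difference are the only comparisons described. The full protocol may define the criterion, but the published rule makes the method depend on the results and gives no margin.

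**The 71%.** A reader might take it as the probability of entering the cost-only branch. It is not: it concerns FEV1 alone, while the trigger covers clinical results generally and side effects. If any one significant outcome left the branch, and ten further efficacy outcomes were null and independent, the figure would be 0.709 × 0.95¹⁰ = 42%, before side effects.

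**Chance switching.** With no effect on any of the 11 efficacy outcomes, the chance of at least one significant result is 1 − 0.95¹¹ = 43% if independent and 5% if fully correlated. This leaves out side effects and week 4. It shows that the choice of method is unstable, not that a benefit is lost.

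**Uncertainty in the ICER.** The article says that, if necessary, "univariate sensitivity analysis is performed for uncertain variables related to cost and effect". A reader might infer that sampling uncertainty in costs and QALYs will be ignored. A condensed article may leave those methods to the full protocol or analysis plan, so this is not a finding.

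**Impact.** The evaluation is called preliminary, and insurance coverage is a hope rather than a decision resting on this analysis. Nor need CSBHT look merely more costly: medical, non-medical and productivity costs are all counted, so total cost could fall. FEV1 in litres does not translate directly into utility. These points limit the size of the concern but do not repair the rule.

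**Conclusion.** The point holds in limited form. The article fixes a results-dependent rule that presents utility only if a difference is found, and otherwise compares cost alone. It gives no criterion for deciding that there is no difference, and the design offers only tests of difference. Followed as written, the rule can set a real effect to zero.

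The litre figures illustrate this for FEV1 only. They rest on an SD borrowed from a study of another product with zero pre-post correlation assumed, and on 84 evaluable per arm. How often the rule would misfire under its own multi-outcome trigger cannot be calculated, because no endpoint is named. The primary FEV1 analysis and the clinical conclusions are unaffected. This should be corrected, but it does not threaten the trial.

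**What to change.** State that the cost-utility analysis will be done whatever the clinical test results, reporting incremental cost and incremental QALYs from the EQ-5D-5L at weeks 0, 4 and 8. Then either remove the cost-minimisation branch, or allow it only when the confidence interval for a named effect measure lies wholly within a pre-specified, justified equivalence margin. If FEV1 were that measure, the second option would rarely be reachable at this sample size unless the margin were wide or the SD well below 0.823 L. Reconcile the two names for the alternative method, cost-utility and cost-effectiveness, so that the effect measure in the ICER is clear.

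The cost is a change of wording and a small amount of extra analysis. The EQ-5D-5L and cost data are already to be collected, so no visit, assessment or participant is added.

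### The economic section states no baseline adjustment for the incremental QALY; adjusting for the baseline EQ-5D-5L already collected would make the ICER denominator more precise at no cost

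*Protocol article*

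**What the plan says.** All of the following is in the protocol article, mostly under Economic evaluation.

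- The ratio: "The ICER is calculated by dividing the increment in cost compared with the control group by the increment-in-effect". It is computed only if the clinical results differ between arms; otherwise a cost-minimisation analysis is done.
- Shown beside it: "the total cost and total utility of each group intervention is presented to confirm the overall scale".
- The horizon: "The analysis period is identical to that of the clinical trial based on the results of the fourth and eighth weeks".
- The utility data: participants "self-complete the EQ-5D at baseline, week 4, and week 8", and "the Korean version of the EQ-5D-5L with proven validity is utilized".
- The QALY: "quality-adjusted life years were calculated based on the value assessment results" of a Korean valuation study. No formula turns the three utilities into a QALY.
- The status: "This study serves as a preliminary investigation for economic evaluation in tandem with a clinical trial".

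Under Statistical analysis (Effectiveness outcomes), the default comparison is an independent t-test or Mann–Whitney test. ANCOVA is used only when a baseline difference between arms is significant. The outcomes listed there are lung function, FeNO, ACT, AQLQ, blood markers and rescue medication. EQ-5D and QALYs are not among them.

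**The concern.** A QALY over the trial period is an area under each participant's utility curve. If the area starts at week 0, the baseline value is itself part of the QALY. If only weeks 4 and 8 count, baseline still enters through the correlation within a person. Either way, part of a chance difference in baseline utility appears in an unadjusted difference between arms, including an imbalance too small to reach significance.

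This matters more here than for most outcomes because the horizon is 8/52 of a year. The QALY difference is bound to be very small, and it is the denominator of a ratio. A modest shift can move the ICER a long way. Cost-effectiveness is one of the trial's stated aims, and the Introduction links the trial to future insurance coverage.

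**Working it through.** **Plan's own figure.** The article gives no precision figure for EQ-5D, QALYs or the ICER, so there is none to reproduce. From Sample size I take only the 168 evaluable participants, or 84 per arm.

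**Assumptions, none from the article.** Trapezoidal QALY; the same utility SD at each visit; correlation ρ between visits of 0.3, 0.5 or 0.7, either equal for all pairs or AR(1); utility SD 0.10 to 0.20 where an SD is needed.

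**QALY.** With T = 8/52 = 0.154 year:

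QALY = T × (0.25·u0 + 0.5·u4 + 0.25·u8)

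**Variance and covariance with baseline.** In units of T²·SD² and T·SD²:

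- Equal correlation: V = 0.375 + 0.625ρ; c = 0.25 + 0.75ρ
- AR(1): V = 0.375 + 0.5ρ + 0.125ρ²; c = 0.25 + 0.5ρ + 0.25ρ²

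Regression on baseline removes the share R² = c²/V of the variance and multiplies the standard error by √(1 − R²).

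| ρ | Structure | c | V | R² | SE factor | SE cut |
|---|---|---|---|---|---|---|
| 0.3 | equal | 0.475 | 0.563 | 0.40 | 0.77 | 23% |
| 0.5 | equal | 0.625 | 0.688 | 0.57 | 0.66 | 34% |
| 0.7 | equal | 0.775 | 0.813 | 0.74 | 0.51 | 49% |
| 0.3 | AR(1) | 0.423 | 0.536 | 0.33 | 0.82 | 18% |
| 0.5 | AR(1) | 0.563 | 0.656 | 0.48 | 0.72 | 28% |
| 0.7 | AR(1) | 0.723 | 0.786 | 0.66 | 0.58 | 42% |

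A simulation of 4,000 trials at ρ = 0.7, equal correlation, SD 0.15 and 84 per arm gave a factor of 0.51. Both estimators averaged close to zero when the true difference was zero, so neither showed bias.

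**Only weeks 4 and 8 used, equally weighted, equal correlation.** R² = ρ² / ((1 + ρ)/2). At ρ = 0.3 this is 0.09/0.65 = 0.14, a cut of 7%. At ρ = 0.7 it is 0.49/0.85 = 0.58, a cut of 35%.

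**Effect taken as change from baseline.** The imbalance then enters with the opposite sign. Adjustment still helps: the factor is 0.74 at ρ = 0.3, 0.82 at 0.5 and 0.90 at 0.7 (equal correlation).

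**Size of an ordinary imbalance.** The SE of the baseline difference is SD × √(2/84): 0.015, 0.023 and 0.031 for SD 0.10, 0.15 and 0.20. The 95% chance ranges are ±0.030, ±0.045 and ±0.060. An imbalance of 0.02 is therefore unremarkable. It shifts the unadjusted incremental QALY by T × c × 0.02, which under equal correlation is:

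- ρ = 0.3: 0.154 × 0.475 × 0.02 = 0.0015
- ρ = 0.7: 0.154 × 0.775 × 0.02 = 0.0024

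At SD 0.15 the unadjusted SE, T × SD × √(2V/84), is 0.0027 (ρ = 0.3) to 0.0032 (ρ = 0.7). Adjusted, it is 0.0021 to 0.0016.

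**Against an assumed gain.** A utility gain of 0.03 at weeks 4 and 8 gives 0.75 × 0.154 × 0.03 = 0.0035 QALY. The 0.02 imbalance then shifts the estimate by 0.0015/0.0035 to 0.0024/0.0035, about 42% to 69% of the gain using unrounded values. If the gain were 0.06, these shares would halve to about 21% to 34%.

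**The case against.** The strongest objection is that the article never says the difference is unadjusted. The quoted sentence is the generic definition of an ICER, and a regression-adjusted increment satisfies it fully. An article condenses a longer protocol and analysis plan, which may specify the estimator, and the economic work is called preliminary. The denominator is not even fixed as a QALY, because the section also speaks of cost-effectiveness and allows clinical measures in the analysis.

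Much of this stands. A reader might infer three stronger things that the document does not support:

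- **That the plan prescribes an unadjusted difference.** It prescribes no estimator. The group totals accompany the ICER to show scale and are not stated to be its denominator.
- **That baseline EQ-5D has no role.** Its collection at baseline is required for this evaluation. The sentence on the fourth and eighth weeks describes the analysis period and does not exclude baseline.
- **That the result would be biased.** Under 1:1 randomisation an imbalance is chance. It adds variance, which a correct interval for the unadjusted difference already reflects. The harm is lost precision and an estimate that is off in the particular sample drawn.

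The sizes also rest on outside assumptions, and equal correlation is the more favourable structure for adjustment.

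The objection does not remove the practical point. The only effect quantities described for presentation by arm are totals. The article's default elsewhere is an unadjusted comparison, and its conditional fallback does not reach EQ-5D. An analyst who followed this text would most naturally take a simple difference.

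**Conclusion.** The point holds as a free improvement, not as an error in the plan. No baseline adjustment is stated for the incremental QALY, and the natural reading of the text gives an unadjusted difference. That difference would be unbiased over randomisations but less precise than it need be, and it would move with any chance imbalance in baseline utility.

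For a trapezoidal QALY with ρ from 0.3 to 0.7, the avoidable part of the standard error is about 23% to 49% under equal correlation and 18% to 42% under AR(1). It is less if only weeks 4 and 8 are used. The direction does not depend on the utility SD or the expected gain. The absolute QALY figures, and the shift as a share of the gain, depend on both, and the article supplies neither.

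**What to change.** State in the analysis plan, before unblinding, that when the cost-utility analysis is performed:

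1. Each participant's QALY is the area under the EQ-5D-5L utility at weeks 0, 4 and 8.
2. The incremental QALY is the arm coefficient from a regression of QALY on arm and baseline EQ-5D-5L utility. The adjustment is always made and does not wait for a significant baseline test.
3. That adjusted difference is the ICER denominator.
4. The unadjusted totals per arm remain as description.

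The cost is one regression and a few lines of text. Baseline EQ-5D-5L is already scheduled, so no new data or visits are needed.

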### Data collection, management and monitoring

Investigators receive comprehensive training on protocol adherence, processes for measuring outcomes, and data recording to ensure the validity and reliability of the data. All data will be entered into the electronic CRF under the supervision of trained investigators. To ensure data accuracy, research associates will conduct thorough verification between CRF data and source documents, resolving any discrepancies. The researcher will contact participants who do not visit within the specified time frame by phone as a reminder. Participants will receive monetary incentives at each visit to encourage participation and completion of follow-up.

A separate space is prepared to preserve the various data and records related to the conduct of clinical trials, ensuring their security. Researchers will transfer clinical trial-related records and materials to the custodian of the trial conduction institution, according to relevant regulations, for preservation for three years following the completion of the trial, except for those with a specific preservation period set by other laws. Furthermore, trial conduction institutions must establish precautions to prevent these materials from being prematurely damaged or lost due to unforeseen incidents. Upon conclusion of the research, the original data collected and acquired during the clinical trial, CRF, and other research processes will be preserved separately in accordance with the regulations dictated by the Institutional Review Board of Kyung Hee University Korean Medicine Hospital.

All documents related to the clinical trial, such as CRF, will be recorded and distinguished using subject identification codes instead of patient names. The source documents associated with this research will be stored in a separate space fitted with a locking device, or on a computer with restricted access. Access to the database is limited to one monitor and the principal investigator. The research will be performed in compliance with the relevant regulations and ethical guidelines pertaining to the protection of subjects, as stipulated by each hospital.

Monitoring is carried out in clinical trials to safeguard the rights and welfare of the subjects; ensure the accuracy, completeness, and verifiability of the reported clinical trial data by cross-referencing with source documents; and confirm the trial's compliance with the approved protocol, clinical trial management standards, and implementation rules. The Clinical Trial Centers at Kyung Hee University Korean Medicine Hospital or Inha University will assign the monitoring task to HelpTrial Inc. (Seoul, Republic of Korea), a clinical research organization. HelpTrial Inc. will conduct regular institutional visits or phone calls, free from any conflicting interests. During these visits, the monitor inspects the participants’ original records, procedural management records, and data storage. The monitor closely oversees the progression of the clinical trial and collaborates with researchers to address any issues. The timing of these visits is determined through mutual agreement between the researcher and the monitor. The researcher is also required to allow monitoring access to the subjects' original documents to verify the data recorded in the CRF, as stipulated in the clinical trial management standards and implementation rules. Findings are reported directly to the principal investigator, ensuring transparency and accountability throughout the study. No interim analysis will be performed.

